#### Home-visit structure [63]

Each home visit is structured to include: a) warm-up period, b) review of the last lesson, c) check on past referrals, d) teaching lesson content, e) activities that model/practice lesson content and help set goals, f) participant review and summary of key lesson points, g) question and answer period, h) plans for homework or referrals, and i) setting up next appointment.

#### Lesson frequency and duration

FSN consists of 36 comprehensive lessons delivered bi-weekly from 28 weeks gestation until birth, weekly from birth to 3 months postpartum, bi-weekly from 3 to 6 months postpartum, and monthly from 6 to 18 months postpartum. Each visit is expected to take up to 60 min. Dosage is based on past evidence that effective home-visiting programs have generally planned for ~ 60 visits over a 1- to 5-year period and aimed to deliver between 32 and 56% of these visits (range 22–33 visits) [67]. Past Family Spirit trials established feasibility of proposed schedule [63].

### Control condition

#### Injury prevention education (IPE)

Mothers randomized to the control condition receive eight educational lessons on the following injury prevention topics: 1) vehicle safety for infants and mothers; 2) scald burns; 3) smoke alarms; 4) home safety; 5) poison storage; and 6) animal bites. These topics are supported by epidemiological data around prevalent injuries in the participating communities. NA populations, including study participants, experience injury disparities, particularly in early childhood. Thus, the control condition was selected as ecologically meaningful to community well-being, while non-contaminating to the intervention condition. Injury prevention education provided to the control group is kept completely separate from the intervention education. Lessons are delivered in the same format as the FSN lessons, by trained Family Health Liaisons (FHLs) in the home of the participant or in a private place of their choosing.

#### Lesson frequency and duration

The IPE lessons occur at the same time points as the following assessments: 36 weeks gestation, 2 weeks postpartum, and at 2, 4, 6, 9, 12 and 18 months postpartum. Each lesson visit is expected to take up to 30 min.

### Optimized standard of care (OSC)

Both the intervention and the control groups will receive OSC, which consists of transportation assistance to prenatal appointments (up to 6) and well-baby clinic appointments (up to 8) as recommended by the IHS and AAP. Both FHCs and FHLs provide rescue services through linkages to community agencies as needed. They often act as advocates for the mothers and families they serve to connect them to needed resources such as housing and food and nutrition assistance.

### Data collection time points

Our mixed-methods assessment includes maternal self-reports and interviews administered using Research Electronic Data Capture (REDCap) tools hosted at Johns Hopkins University, observations (including maternal/infant anthropometric measurements, infant accelerometry, and home safety assessments), maternal/infant medical chart reviews and maternal/infant blood sample collection (Table 2). REDCap is a secure, HIPAA compliant, web-based application designed to support data capture for research studies. It provides 1) an intuitive interface for validated entry; 2) audit trails for tracking data manipulation and export procedures; 3) automated export procedures for seamless data downloads to common statistical packages; and 4) procedures for importing data from external sources [68].

**Table 2 Tab2:** List of Evaluation Measures

		Pregnancy		Postpartum							
		Baseline	36 weeks gestation	2 weeks post-partum (pp)	2* months pp	4 months pp	6* months pp	9 months pp	12* months pp	18* months pp	24* months pp
Self-Report Interviews											
1. Maternal Demographics	15 min	X	X	X	X		X		X		X
2. Child Feeding Assessment [70]	10–20 min			X	X	X	X	X	X	X	X
3. Maternal Beverage Intake Questionnaire [70]	5 min	X	X		X		X		X	X	X
4. U.S. Household Food Security Survey [71]	3–10 min	X			X		X		X	X	X
5. Brief Infant Sleep Questionnaire (BISQ) [72]	5 min				X		X		X	X	X
Self-Reports											
6. Current Eating Environment Assessment	5 min				X		X		X		X
7. Infant Responsive Feeding Scale [73]	5 min				X		X		X		
8. Toddler Responsive Feeding Scale [73]	5 min										X
9. Baby Eating Behavior Questionnaire [74]	5 min						X				
10. Children’s Eating Behavior Questionnaire – Toddler [75]	5 min								X		
11. Perceptions of Growth Scale [76]	3 min				X		X		X		X
12. Child Physical Activity Assessment	5 min				X	X	X	X	X	X	X
13. Knowledge Questionnaire - Maternal Nutrition, Feeding and Physical Activity Practices	10 min	X			X		X		X	X	X
14. Water Availability Assessment [77]	5 min	X			X		X		X		X
15. Perceived Stress Scale [78, 79]	3 min	X			X		X		X	X	X
16. Centers for Epidemiologic Studies Depression Scale-Revised (CESDR-10) [80]	5 min	X	X	X	X		X		X	X	X
17. Alcohol, Smoking and Substance Involvement Screening Test (ASSIST) [81, 82]	5 min	X							X		X
18. Mastery Scale [83, 84]	5 min	X			X		X		X		X
19. Infant Temperament [76]	3 min				X	X	X	X			
20. Brief Infant Toddler Social Emotional Assessment (BITSEA) [85]	10 min								X	X	X
21. Participant Satisfaction Questionnaire	10 min									X	
22. Injury Assessment	10 min	X							X	X	X
Observations Completed by Study Staff											
23. Toddler Physical Activity Assessment (Accelerometer) [48]	10 min									X	X
24. Maternal Height and Weight	5 min	X			X*				X*		X
25. Child Weight and Length	5 min			X	X	X	X	X	X	X	X
26. Home Safety Environment Scan	5–30 min		X	X				X	X		X
Specimen Collection											
27. Blood Sample Collection – Mothers	5 min			X (delivery)			X				
28. Blood Sample Collection – Infants	5 min			X (delivery)			X		X		
Process Form Completed by Study Staff											
29. Session Summary Form	No participant time burden	ADMINISTERED AT ALL VISITS									
Medical Chart Reviews											
30. Maternal Medical Chart Review	No participant time burden	THROUGHOUT THE STUDY PERIOD									
31. Child Medical Chart Review											
Total Participant Time Burden** (min):		58 min	30 min	75 min	104 min	28 min	114 min	43 min	151 min	98 min	151 min

**Maternal weight only will be collected at these time points*

***The 2-month, 6-month, 12-month, 18-month and 24-month assessments are completed in two sittings, to reduce participant burden. The interviews and observations are completed in the first sitting, and the self-report assessments are completed one week later*

Self-reports, interviews, and observations are conducted in participants’ homes or another private location, with data recorded in tablet computers. Medical chart reviews will be completed independently by study staff after 24 months postpartum. Blood samples are collected in the hospital at delivery and in participants’ homes or another private location at two other time points (6 and 12 months postpartum). If it is not possible to collect maternal/infant blood in the hospital at delivery, maternal blood may be collected between 36 weeks gestation and delivery, and infant blood may be collected up to one week after delivery. Blood samples are being analyzed for: fasting glucose, insulin, leptin, adiponectin, lipid panels, and C-reactive protein. All study participants will be assessed at 11 time points: baseline (< 32 weeks gestation), 36 weeks gestation, delivery (blood sample collection only), 2 weeks, 2 months, 4 months, 6 months, 9 months, 12 months, 18 months, and 24 months postpartum. Family Health Liaisons (FHLs) work together with Independent Evaluators (IEs) to administer assessments to both groups *with the exception of the baseline assessment* (conducted by FHLs only). IEs are blind to participants’ randomization status and conduct key interview and observational assessments to ensure objective data collection. IEs also help study staff complete medical chart reviews.

Participants receive a gift card or gift package upon completion of the following assessment time points: baseline, 36 weeks gestation, 2 weeks postpartum, and 2, 6, 12, 18, and 24 months postpartum. Total possible remuneration for participants in the study is $160 in gift cards and a gift package valued at $10 for participant in assessments. In addition, enrolled mothers will be given a $15 gift card for each blood sample collected from the mother or infant. This occurs at three time points for infants (delivery, 6 months, and 12 months) and two time points for the mothers (delivery and 6 months). Total possible remuneration for participants in the study is $75 in gift cards for specimen collection. Study participants can receive up to $235 in gift cards and a gift package valued at $10 if they participate in all assessments and blood collections.

### Outcomes

Selected measures are being used to assess intervention impact on the following primary and secondary outcomes.

#### Primary outcomes

Group differences in percentage of mothers who meet breastfeeding and complementary feeding recommendations and percentage of mothers who introduce SSBs over time as assessed by the Child Feeding Assessment. From 2 weeks to 24 months pp., mothers are asked questions from an adapted version of the Pre-School-Aged Beverage Intake Questionnaire (BEVQ-15) in addition to items developed by the study team and based on previous studies conducted by the co-investigators. The assessment will be used to assess feeding practices, duration of exclusive and non-exclusive breastfeeding, timing of introduction of complementary foods and types of first foods, and introduction of SSBs.Group differences in mean scores for infant feeding style subscales assessed using the Infant Feeding Behavior Questionnaire, which asks mothers to indicate how often they engage in specific feeding behaviors to assess maternal feeding styles from 2 month to 12 months pp. There are five subscales that are used to assess maternal feeding style: Responsive, Forceful, Restrictive, Indulgent, and Uninvolved. There is no total scale score. The assessment is valid and reliable. This 24-item scale is scored with a 3-point Likert scale. A mean score is calculated for each subscale, with a range of 0 to 2. The range of the 3-point Likert scale is as follows: 0 (never), 1 (sometimes), 2 (always). Higher scores reflect higher levels of feeding style indicated by a given subscale.Group differences in in mean scores for toddler feeding style subscales assessed using the Toddler Feeding Behavior Questionnaire, which asks mothers to indicate how often they engage in specific feeding behaviors to assess maternal feeding styles at 24 months pp. There are five subscales that are used to assess maternal feeding style: Responsive, Forceful, Restrictive, Indulgent, and Uninvolved. There is no total scale score. The assessment is valid and reliable. This 27-item scale is scored with a 3-point Likert scale. A mean score is calculated for each subscale, with a range of 0 to 2. The range of the 3-point Likert scale is as follows: 0 (never), 1 (sometimes), 2 (always). Higher scores reflect higher levels of feeding style indicated by a given subscale.Group differences in children’s consumption of fruit and vegetable intake from SSBs, snacks, and desserts over time as assessed by the USDA Household Food Security Survey. From 6 months to 24 months pp., mothers are asked questions about her child’s fruit and vegetable consumption beginning at 6 months postpartum and at all subsequent time points. These items have been added to a standardized 18-item USDA food security survey, the U.S. Household Food Security Survey, that measures household food security. Fruit and vegetable consumption will be measured by asking mothers how much and how often her child eats fruits and vegetables and whether she feels she is able to provide her child with the fruits and vegetables he or she needs. To obtain weekly fruit and vegetable servings consumption, the number of times per week fruits or vegetables are consumed will be multiplied by the number of servings consumed each time. Serving size will be age adjusted.Group differences in children’s PA levels as assessed by accelerometry. At 18- and 24-months pp., children’s PA will be measured objectively using accelerometry. We will use the Actical accelerometer, a small waterproof device (28x27x10mm) weighing 17 g, which is omnidirectional (sensing motion in all planes) and integrates the degree and intensity of motion. We will use procedures co-investigators have used successfully in previous studies of young adolescents, toddlers and their mothers, placing the accelerometer on the non-dominant ankle with a non-removable, reinforced hospital band worn next to the skin, under socks, for 7 consecutive days. Accelerometers will be attached on the day of the 18- and 24-month assessment battery and removed one week later. Data will be collected in 1-min epochs. The time-stamped data will be examined. Summary statistics will include average and total activity counts and minutes in MVPA.Group differences in children’s reported PA, screen time and other sedentary activities over time as assessed by the Child Physical Activity Assessment from 2 months to 24 months pp. This 14-item self-report assessment includes questions about tummy time, crawling, walking, sedentary behavior and screen time for infants and toddlers. Questions were compiled based on a body of literature related to assessing infant/toddler physical activity.Group differences in children’s mean BMI z-scores over time (2 weeks to 24 months pp) as assessed through child weight and length measurements over time. Description: Child weight (to the nearest ounce) and recumbent length (to the nearest 1/8 in.) are measured using a digital scale and a recumbent measuring board (in accordance with IHS guidelines). All measurements will be taken in triplicate, removing the most disparate measurement, and averaging the remaining two. Averages will be used to calculate BMI z-scores using age- and sex-specific WHO Child Growth Standards.

#### Secondary outcomes

Group differences in levels of maternal stress over time as assessed by the Perceived Stress Scale 4 (PSS-4). Completed by mothers from pregnancy to 24 months pp., the 4-item questionnaire assesses maternal stress. It is scored with a five-point Likert scale. The range of the five-point Likert scale is as follows: 0 (never), 1 (almost never), 2 (sometimes), 3 (fairly often), 4 (very often). We will reverse scores for items 2 and 3. On these questions, the scores will be as follows: 4 (never), 3 (almost never), 2 (sometimes), 1 (fairly often), 0 (very often). Scores for each item will be summed to get a total score. The lowest score is 0 and the highest score is 16. Higher scores are correlated to more stress (worse outcome).Group differences in depression scores over time (pregnancy to 24 months pp) as assessed by the Centers for Epidemiological Studies Depression Scale-Revised-10 (CESDR-10). The 10-item questionnaire is a validated adapted version of the CESD-R (which has been utilized to assess depression with Navajo mothers) to screen for depression in adolescents. The questionnaire asks participants to rate how often over the past two weeks have they experienced symptoms associated with depression, such as restless sleep, poor appetite, and feeling sad. Response options range from 0 to 4 for each item, with 0 = *not at all or less than 1 day in the last 2 weeks*, 1 = *1–2 Days*, 2 = *3–4 Days*, 3 = *5–7 Days*, 4 = *Nearly every day for 2 weeks*. Scores for each item will be summed to get a total score. Scores range from 0 to 40, with high scores indicating greater depressive symptoms (worse outcome). A CESD-R score of 8 or greater indicatesGroup differences in alcohol and drug use over time (pregnancy to 24 months pp) as assessed by the Alcohol, Smoking and Substance Involvement Screening Test (ASSIST). Adapted from the WHO ASSIST questionnaire covering 10 main substance groups, this 15-item questionnaire screens for all levels of problem or risky substance use (alcohol, illegal drugs, and prescription drugs). A risk score is provided for each substance, and scores are grouped into low, moderate, or high risk. Only items 2–7 and 9–14 are scored. Each of these questions has a set of responses to choose from, and each response has a numerical score. The scores from questions 2–7 are added together, and the scores from questions 9–14 are added together to produce an ASSIST risk score for each substance that falls into one of three categories: low, moderate, or high substance-related risk. Participants with risk scores 3 or less (10 or less for alcohol) are at lower risk of problems related to their substance use. Participants scoring between 4 and 26 (11 and 26 for alcohol) are at moderate risk of health and other problems and may be experiencing some of these problems right now. A score of 27 or higher for any substance suggests that the participant is at high risk of dependence or is dependent on that substance and is probably experiencing health, social, financial, legal, and relationship problems as a result of their substance use.Group differences in how infant biologic measures of metabolic health (fasting glucose, insulin, leptin, adiponectin, lipids panels, and c-reactive protein) at delivery and 6 months postpartum correlate to maternal biologic measures of metabolic health. Blood specimens are collected from mothers at delivery and 6 months postpartum. Blood specimens are collected from infants at delivery (cord blood), 6 and 12 months postpartum. Laboratory testing will be completed to assess levels of fasting glucose, insulin, leptin, adiponectin, lipids panels, and c-reactive protein in mothers and babies to examine how infant metabolic health relates to maternal metabolic health at delivery, and whether there are between group differences in this relationship over time. In all cases, higher levels indicate poorer metabolic health.Group differences in infant metabolic health at delivery, 6 and 12 months postpartum. Blood specimens are collected from infants at delivery (cord blood), 6 and 12 months postpartum. Laboratory testing will be completed to assess levels of fasting glucose, insulin, leptin, adiponectin, lipids panels, and c-reactive protein in infants to examine whether there are between group differences in infant metabolic health at delivery and over time (delivery to 12 months postpartum). In all cases, higher levels indicate poorer metabolic health. In addition, results will be used to determine whether infants are insulin resistant and/or leptin insensitive (these will be dichotomous outcomes) and between group differences will be assessed at delivery and over time (delivery to 12 months postpartum).Examination of whether group differences in infant metabolic health at delivery, 6 and 12 months postpartum are moderated or mediated by sociodemographic, biological (e.g. pre-pregnancy BMI, gestational weight gain, gestational diabetes, etc.), and psychosocial characteristics of mothers at baseline). Blood specimens will be collected from infants at delivery (cord blood), 6 and 12 months postpartum. Laboratory testing will be completed to assess levels of fasting glucose, insulin, leptin, adiponectin, lipids panels, and c-reactive protein in infants. In all cases, higher levels indicate poorer metabolic health. Analyses will be conducted to determine whether between group differences in metabolic health at delivery and over time (delivery to 12 months postpartum) are moderated or mediated by sociodemographic, biological, and psychosocial characteristics of mothers at baseline.

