#### Primary aims analysis

We will conduct intent-to-treat analyses to estimate effects of the FSN + OSC intervention compared to the OSC + IPE control condition on early childhood obesity and related risk factors. Separately, we will examine the effects of intervention dose and conduct a “completer analyses” on subjects receiving minimum intervention dose (> 50% of lessons). Analyses will be adjusted for multiple comparisons using Bonferonni corrections.

Demographic and outcome variable distributions will be examined to assess whether comparability between intervention groups at baseline was achieved through randomization. For time discrete outcome measures, t- tests or chi-square tests will be used to test whether the intervention impacted each outcome in unadjusted analyses. Multiple linear or logistic regression will be used to test the impact of the intervention on each outcome, controlling for baseline demographic characteristics where necessary and examining potential moderators in secondary analyses. For time varying outcome measures we will examine the impact of the intervention by analyzing between group differences at each time point using t-tests and multiple regression analyses. For those outcomes with sufficient power, multi-level mixed-effects regression with a random effect at the individual level and appropriate variance structures, and an interaction term for treatment x child age will be used to examine change over the course of the intervention period for the intervention and control groups.

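### PSS-4, CESDR-10 and ASSIST are measured before randomisation, but the stated analysis does not name the mother's own baseline score as a covariate, so a free gain in precision is not secured

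*Protocol article*

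**What the plan says.** **Outcomes.** Under Secondary outcomes, stress is "Group differences in levels of maternal stress over time as assessed by the Perceived Stress Scale 4 (PSS-4"), and "Completed by mothers from pregnancy to 24 months pp., the 4-item questionnaire assesses maternal stress". Depression is "Group differences in depression scores over time (pregnancy to 24 months pp"). Substance use by ASSIST has the same window, and its scores are grouped as low, moderate or high risk for each substance.

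**Timing.** Table 2, under Data collection time points, gives these visits:
- "15. Perceived Stress Scale [78, 79]": baseline, then 2, 6, 12, 18 and 24 months.
- "16. Centers for Epidemiologic Studies Depression Scale-Revised (CESDR-10) [80]": baseline, 36 weeks' gestation, 2 weeks, then 2, 6, 12, 18 and 24 months.
- "17. Alcohol, Smoking and Substance Involvement Screening Test (ASSIST) [81, 82]": baseline, 12 and 24 months.

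The Randomization section places allocation after the baseline assessment. The baseline scores are therefore true pre-randomisation values.

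**Analysis.** Primary aims analysis handles time-varying outcomes by "analyzing between group differences at each time point using t-tests and multiple regression analyses". The covariates it names are demographic characteristics at baseline, to be used if needed. For outcomes with enough power it adds a mixed model with a random effect per individual and a treatment-by-child-age interaction. It also says that baseline distributions of outcome variables will be inspected for comparability. The other analysis section covers only the biologic measures.

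**The concern.** A baseline score on the same scale is usually among the better predictors of a later score. Here it has already been collected for three maternal outcomes. A per-visit t-test cannot use it. The per-visit regressions name only demographics, and leave even those to a judgement of need. As written, a chance imbalance in baseline stress or depression would be seen in the comparability check, and no stated rule would then adjust for it.

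What is at stake is precision: wider intervals and lower power than the collected data allow, on outcomes for which the article states no power. A smaller matter is that the choice of covariates is left open until the data have been seen.

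**Working it through.** **Inputs from the article** (Sample size calculation and statistical analysis, Table 3): 169 mothers per arm, 16% loss by 24 months, 80% power, 5% significance, detectable difference 0.33 SD for BMI z-score. Two-sided testing is assumed because sidedness is not stated.

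**Input not in the article:** r, the correlation between baseline and follow-up score. It is assumed and shown over a range.

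**Step 1. Reproduce the design figure.**
- Evaluable per arm: 169 × 0.84 = 141.96, about 142.
- Detectable difference = (1.960 + 0.842) × √(2/142) = 0.332 SD, against the stated 0.33.

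The article obtained the BMI z-score figure by simulation, and the closed form agrees with it. The figure is used here only as a benchmark for an effect with 80% unadjusted power. It is not a claim about stress, depression or substance use.

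**Step 2. Gain from the baseline score at one visit.** For a continuous score, ANCOVA multiplies the variance of the arm difference by 1 − r². The detectable difference becomes 0.332 × √(1 − r²). Power for the 0.332 SD effect is Φ(2.802/√(1 − r²) − 1.960). The equivalent number of unadjusted mothers is 284/(1 − r²).

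| r (assumed) | Variance cut | Detectable difference | Power | Equivalent unadjusted N (actual 284) |
|---|---|---|---|---|
| 0 | 0% | 0.332 SD | 80% | 284 |
| 0.2 | 4% | 0.326 SD | 81.6% | 296 |
| 0.3 | 9% | 0.317 SD | 83.6% | 312 |
| 0.4 | 16% | 0.305 SD | 86.4% | 338 |
| 0.5 | 25% | 0.288 SD | 89.9% | 379 |
| 0.6 | 36% | 0.266 SD | 93.8% | 444 |

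**Step 3. Gain for an average over visits.** Take the mean of the five postpartum PSS-4 visits with an equal correlation r between all visits. The unadjusted variance factor is (1 + 4r)/5, and adjustment removes r².
- r = 0.3: 0.09/0.44 = 20.5%.
- r = 0.4: 0.16/0.52 = 30.8%.
- r = 0.6: 0.36/0.68 = 52.9%.

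**Step 4. Does the stated mixed model already deliver this?** Not necessarily. Suppose baseline enters as an outcome point with a free arm difference there and separate visit effects. With complete data, the arm-by-visit contrast is then a difference in change scores, with variance factor 2(1 − r). That is 1.6, 1.2 and 0.8 at r = 0.2, 0.4 and 0.6, against 0.96, 0.84 and 0.64 for ANCOVA. The gain needs the arm means to be held equal at baseline, and the article does not state this.

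**The case against.** The opposing case has real force, and several stronger readings that a reader might infer do not hold.

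- **That the plan excludes the baseline score.** The article nowhere says so. The covariate wording sits under the primary aims, where child outcomes have no baseline. No model is written specifically for the maternal psychosocial outcomes, and the full analysis plan is not shown. The supportable statement is that the score is not named.
- **That per-visit tests are the only method.** They are not. The mixed model follows in the same paragraph and could take the baseline value as a repeated measure. However, it is reserved for outcomes with sufficient power, none of the six powered outcomes is a maternal psychosocial scale, and its time axis is child age.
- **That an arm difference will be tested at baseline.** Pregnancy to 24 months reads more naturally as the collection window than as a list of tests. For CESDR-10 the 36-week visit is in pregnancy and after randomisation.
- **That the gain is large.** The article gives no correlation. PSS-4 has four items and follow-up reaches two years postpartum, so a low r is plausible. At r = 0.2 to 0.3 the gain at one visit is only 4% to 9% of the variance.
- **That the comparison is biased.** An unadjusted comparison in a 1:1 randomised trial is unbiased, and its standard error already allows for chance imbalance.

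What survives is narrower. The article does describe covariates and methods, and what it describes leaves out the one covariate most likely to help these scales.

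**Conclusion.** The point stands as a free improvement for secondary outcomes. It is not an error, and no stated figure is wrong.

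For a continuous PSS-4 or CESDR-10 score, the variance reduction at a visit is about r²: 4%, 16% and 36% at r = 0.2, 0.4 and 0.6. For an effect with 80% unadjusted power at 142 per arm, power becomes about 82%, 86% and 94%. These figures rest on an assumed r, two-sided 5% testing, the planned 16% loss, and a linear relation with similar variance in the two arms. The 1 − r² formula does not carry over directly to ASSIST risk categories, though adjusting for baseline ASSIST is still sensible.

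**What to change.** For PSS-4, CESDR-10 and ASSIST, pre-specify that:

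1. arms are compared at post-randomisation visits only;
2. every such comparison adjusts for the mother's own baseline score whatever the observed balance, by ANCOVA or by a longitudinal model with arm means constrained equal at baseline;
3. if ASSIST is analysed by risk group, an ordinal or logistic model with baseline category is used;
4. simple change scores are not used as a substitute, since at one visit they are less precise than no adjustment when r is below 0.5.

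Apply the same rule to other maternal measures with a baseline column in Table 2, such as beverage intake and the knowledge questionnaire. The data are already scheduled for collection, so the cost is a few sentences in the analysis plan. The change should be made before outcome data are compared by arm.
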